## Background

Delirium is a neuropsychiatric disorder characterized by an acute onset of confusion, inattention, and a change in level of consciousness that tends to fluctuate during the day [1,2]. The incidence of delirium in intensive care unit (ICU) patients is high [3-6], approximately 30–50%. Further, its occurrence is associated with detrimental outcome, including prolonged duration of mechanical ventilation, increased ICU and hospital length of stay (LOS) [4-6], unplanned removal of tubes and catheters [6], increased mortality [6-8], and long-term cognitive disturbances [9,10]. Therefore, a strategy that can prevent delirium in high-risk patients may also decrease short-term (i.e., 28-day) mortality.

The first step in the management of delirium is to treat the underlying disease. If delirium does not subside, haloperidol is the most frequently used pharmacologic treatment of delirium. However, this drug may also be used to prevent delirium. In non-ICU patients, beneficial effects have been reported of prophylactic haloperidol in older and surgical patients [11,12]. For critically ill patients, data concerning prevention with anti-psychotic drugs are scarce and inconsistent [13-15]. In one retrospective cohort study, ICU patients who received haloperidol were found to have a lower mortality rate compared to ICU patients that did not receive haloperidol [16]. Only one prospective, randomized trial in critically ill patients is available, showing that haloperidol prophylaxis in non-cardiac surgical ICU patients had beneficial effects on delirium incidence and the number of delirium free-days [17]. However, only a very low dose, for 12 h infusion of haloperidol was administered and many of the patients were in the ICU for less than 24 h [17]. Thus, there are no large, definitive trials that have studied the effect of haloperidol prophylaxis in ICU patients.

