### Study population

#### **
*Inclusion criteria*
**

All consecutive critically ill patients admitted to the ICU aged ≥18 years at the time of ICU admission and with an expected length of ICU stay of over one day will be included as informed consent is obtained.

Data from patients that are included in the study, but who do not receive any study drug and are discharged from the ICU within 24 h will be discarded from further analysis. Patients who received at least one dose will remain in the study and patients in whom study medication had to be halved or stopped, e.g., because of prolonged QTc time or other side effects, will remain allocated to their study group and analyzed on an intention-to-treat basis.

#### **
*Exclusion criteria*
**

The following will be considered exclusion criteria: no informed consent obtained; history of epilepsy, Parkinson’s disease, hypokinetic rigid syndrome, dementia or alcohol withdrawal syndrome; patients admitted to the ICU for any other neurological disease (including post-cardio-pulmonary resuscitation patients, and patients admitted with coma due to overdose); patients treated with anti-psychotic therapy over the last 30 days prior to ICU admission; prolonged QTc-time (>500 msec) or history of clinically relevant ventricular arrhythmia in last 12 months; pregnancy/breast feeding; documented delirium prior to ICU admission; reasons that impair delirium assessment with the CAM-ICU (serious auditory or visual disorders, unable to understand Dutch or English; severely mentally disabled; serious receptive aphasia); ICU-stay less than one day; moribund and not expected to survive two days; known allergy to haloperidol.

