### Objectives

Definitions of variables in objectives are reported in Table 1.

**Table 1 T1:** Definition of study objectives

**Objective**	**Definition**
*Survival days in 28 days*	Number of days that patients survive in 28 days. All patients will be classified as either ‘alive at study day 28’ or, if dead, ‘dead at study day 28’ on an intention-to-treat basis.
*Delirium diagnosis*	Patients are diagnosed as delirious when they have at least one positive CAM-ICU screening during their complete ICU stay. Patients who were not delirious during their ICU-stay are considered as non-delirious patients.
*Delirium-and-coma-free days in 28 days*	Number of days that the patient is alive and not delirious and not in coma over 28 days starting from the day of inclusion. A delirium-and-coma-free day is defined as a negative CAM-ICU screening with a Richmond Agitation Sedation Score (RASS) greater than (more alert than) -3/-4/-5 during a day. In case a delirious patient is discharged to the ward, a delirium-free day is defined as a delirium observation scale score [30] of less than 3 during a complete day.
*Duration of mechanical ventilation*	Time in days that the patient is on the mechanical ventilator. If the patient is ventilated mechanically several times during one ICU admission, then the ventilator times are added. Both invasive and non-invasive ventilation will be registered. Ventilator-free days (in 28 days) will be calculated.
*Incidence of re-intubation*	Patients who need to be intubated within 28 days from randomization, following a previous extubation, irrespective of the reason for re-intubation, are counted as incident case for re-intubation.
*Incidence of ICU readmission*	Patients who need to be readmitted to the ICU during within 28 days from randomization, irrespective of the reason for readmission, are counted as incident cases for ICU readmission.
*Side effects*	Drowsiness, agitation, QTc-time prolongation (using 12-leads ECG or monitor strip with Bazett’s formula) and development of extra pyramidal symptoms such as tandem gait, dystonia, tremor, myoclonus, tics, rigidity, akathisia [31], determined daily by physical examination by the intensivist.
*Serious adverse event*	Any untoward medical occurrence or effect at any dose that results in one of the following outcomes and is not classified as a clinical outcome of delirium or the underlying disease using the description above:

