	- death that is not related to the underlying disease or sequel of the underlying disease, or death that is considered by the investigator to be related to study drug
	- prolonged inpatient hospitalization or re-hospitalization
	- a life-threatening experience (that is, immediate risk of dying)
	- persistent or significant disability/incapacity
	- congenital anomaly/birth defect
	- considered significant by the investigator for any other reason
*Sudden unexpected serious adverse reactions*	Unexpected adverse reactions are adverse reactions, of which the nature, or severity, is not consistent with the applicable product information. Adverse reactions are all untoward and unintended responses to an investigational product related to any dose administered.

#### **
*Primary objective*
**

To determine the effect of prophylactic haloperidol use on 28-days survival.

#### **
*Secondary objectives*
**

There are seven secondary objectives:

1. To determine the effect of prophylactic haloperidol use on 90-day survival; survival analysis stratifying for delirium incidence will be performed.

2. To determine the effect of prophylactic haloperidol use on the incidence of delirium.

3. To determine the effect of prophylactic haloperidol use on the number of delirium- and coma-free days in a period of 28 days.

4. To determine the effect of prophylactic haloperidol use on delirium related outcomes: time to successful extubation, incidence of re-intubation, incidence of ICU readmission, and incidence of unplanned removal of tubes and catheters.

5. To evaluate the incidence and severity of side effects of haloperidol prophylaxis.

6. To determine the effect of preventive haloperidol use on quality of life 1 and 6 months following ICU admission compared with a baseline measurement at ICU admission using the Short Form-12 (SF-12) questionnaire.

7. *A priori* defined post-hoc analyses:

a. To determine the preventive effectiveness of haloperidol in different patient groups based on the *a priori* risk to develop delirium: patients with a predicted risk up to 50%, 50–70%, 70–90%, above 90% will be evaluated.

a. To determine the preventive effectiveness of haloperidol in different patient groups: medical/surgical/trauma patients, per acute physiology and chronic health evaluation-II (APACHE-II) score (<20, 20–25, >25)

a. Effectiveness of prophylaxis when delirium is diagnosed based on 1, 2, or more days with positive CAM-ICU scoring.

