### Sample size calculation and statistics

Sample size calculation is based on the difference in survival from our previous prophylactic haloperidol study [19]. In this study, the median survival time in the control group was 18 days. If the true hazard ratio of control patients relative to intervention patients is 0.85, taking into account an accrual time of 90 days with 28 days of follow-up, we will need to study 647 patients per intervention group and 647 control patients to be able to reject the null hypothesis that the experimental and control survival curves are equal with probability (power) 0.80. The Type I error probability associated with this null hypothesis test is 0.05. Taking into account a dropout percentage of 10%, we will include 715 patients per group (Figure 1). A fixed sequence procedure will be followed. First, the highest dosage of prophylactic haloperidol will be compared with placebo using alpha 0.05 (two-sided). Only if H_0_ is rejected, subsequently the lower dosage of prophylactic haloperidol will be compared with placebo. Cox regression analysis will be used to test differences on 28-day survival in the intervention group compared with the placebo group.

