**Figure 1 F1:**
[figure not shown]
CONSORT flowchart of patient enrollment.

A safety, futility, and superiority interim analysis will be performed by the DSMB after 175, 350, 500 (safety and futility) and 1,000 (safety and superiority) patients are included. Differences in serious adverse events between intervention and placebo are used for safety analyses and the primary endpoint 28-day survival is used to determine futility or superiority of intervention or placebo.

After the inclusion of 1,000 patients, superiority will be tested. A proven superiority (*P < 0.003, two-sided)* of any dose of haloperidol over placebo or a proven superiority (*P < 0.003, two-sided)* of placebo over haloperidol determined during the interim analysis will result in an alpha of 0.049 (two-sided) for the final analysis. This alpha distribution was calculated by an independent statistician according to the method of Lan-DeMets cumulative alpha spending function of O’Brien-Fleming alpha spending [36].

Data will be analyzed according to the intention-to-treat principle. For the descriptive statistics, continuous variables will be given as mean with standard deviation or median and inter quartile ranges, depending on their distribution. Normally distributed variables will be tested using Student’s *t*-test for comparison and Mann-Whitney U-tests for non-normally distributed variables. Categorical (and binary) variables will be presented as numbers and percentages and will be analyzed using the χ^2^ test. Survival analyses with Kaplan-Meier curves will be used as graphical representation. Cox proportional hazard regression analyses will be used to estimate the hazard ratio for survival with the use of haloperidol versus placebo. Furthermore, we will perform adjusted analyses for relevant covariates (including delirium, APACHE-II score, age, sex, sepsis, and other differences between the three study groups irrespective of the possible imbalance between the three groups). For this covariate analysis, univariate logistic regression analysis will be performed first in order to test the strength of the relationship. Subsequently, variables significantly associated with the dependent variable will be included in the covariate analyses.

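### The adjusted 28-day and delirium-stratified 90-day survival analyses condition on delirium, a post-randomisation outcome on the assumed causal path, and so can dilute, remove or reverse the treatment effect

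*Protocol article*

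**What the plan says.** The section on sample size and statistics sets out the primary comparison first: "Cox regression analysis will be used to test differences on 28-day survival in the intervention group compared with the placebo group". No covariates are named there. Later in the same section, after the Cox hazard ratio for haloperidol versus placebo, further models are added: "we will perform adjusted analyses for relevant covariates (including delirium, APACHE-II score, age, sex, sepsis", plus other differences between the groups. The rule for entering the model is that "variables significantly associated with the dependent variable will be included in the covariate analyses", after univariate screening. It is not restricted to baseline variables.

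Secondary objective 1, on 90-day survival, adds that "survival analysis stratifying for delirium incidence will be performed".

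Four other places fix what delirium is in this trial:

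- Table 1: "Patients are diagnosed as delirious when they have at least one positive CAM-ICU screening during their complete ICU stay".
- Exclusion criteria: "documented delirium prior to ICU admission".
- Secondary objective 2: "To determine the effect of prophylactic haloperidol use on the incidence of delirium".
- Background: "a strategy that can prevent delirium in high-risk patients may also decrease short-term (i.e., 28-day) mortality".

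**The concern.** The trial asks whether giving prophylaxis, as opposed to placebo, changes survival. By the Background's own reasoning, any benefit runs at least partly through fewer patients becoming delirious. Holding delirium constant in the Cox model, or comparing arms within delirium strata, takes out the part of the effect that runs through it.

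It also breaks the randomised comparison. Patients delirious despite haloperidol need not resemble patients delirious on placebo. If unmeasured severity drives both delirium and death, conditioning on delirium biases the treatment contrast, and the bias can go beyond removing the effect. Two further features make the delirium strata hard to interpret. Under the section on end of study medication, delirium ends study drug and starts open-label haloperidol in every arm, placebo included. An ever/never delirium covariate also requires the patient to live until onset, which brings in time-dependent bias.

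At stake is how the mortality result is read. If prophylaxis works as hypothesised, the adjusted hazard ratio may lie near or above 1 and appear to contradict a true benefit, when it answers a different question.

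**Working it through.** **Is the covariate post-randomisation?** Yes. Table 1 counts any positive CAM-ICU over the whole ICU stay, and delirium documented before ICU admission is an exclusion criterion. Baseline delirium risk is a separate variable, the PRE-DELIRIC score, and it is not among the covariates named.

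**Would the entry rule drop it?** Probably not. The Background reports that delirium is associated with increased mortality, so it is likely to pass a significance screen against death.

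**How large is the effect?** The plan gives no figure for the adjusted analysis, so there is none to reproduce.

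Inputs from the article:
- Delirium 75% (control) versus 65% (prophylaxis), from the earlier high-risk study in the Background.
- Placebo mortality 12%, from the Abstract.
- Median predicted delirium risk of about 35% in the target population, from the Background. The same relative reduction gives 35% × 65/75 = 30.3%.

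Assumptions not in the article:
- Hazard ratio of death with delirium, *h*, of 2 or 3.
- Direct drug effect, *d*, of 1 (none) or 0.9.
- An unmeasured factor that is either absent or raises both the odds of delirium (log-odds 1 to 1.5 per SD) and the death hazard (log-hazard 0.7 to 1 per SD).
- Constant hazards over 28 days, with delirium as a fixed ever/never variable.

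With no common cause, the hazard ratio holding delirium fixed is *d*. The hazard ratio without delirium in the model is approximately

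d × [1 + (h − 1) × 0.65] / [1 + (h − 1) × 0.75].

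- *h* = 2, *d* = 1: 1.65/1.75 = 0.943, against 1.00 when adjusted.
- *h* = 3, *d* = 1: 2.30/2.50 = 0.920, against 1.00 when adjusted.
- *h* = 3, *d* = 0.9: 0.9 × 0.920 = 0.828, against 0.90 when adjusted.

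The large-sample calculation over 28 days used a constant-hazard Poisson equivalent of the Cox model, integrated over the unmeasured factor, with placebo mortality set to 12%. It gives:

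| Setting (75% vs 65% delirium) | Without delirium | With delirium |
|---|---|---|
| Wholly through delirium, *h* = 2 | 0.942 | 1.000 |
| Wholly through delirium, *h* = 3 | 0.918 | 1.000 |
| Same, common cause, *h* = 2 | 0.957 | 1.052 |
| Same, common cause, *h* = 3 | 0.940 | 1.051 |
| Same, stronger common cause, *h* = 3 | 0.955 | 1.085 |
| Partly direct (*d* = 0.9), *h* = 3 | 0.827 | 0.900 |
| Partly direct, common cause, *h* = 3 | 0.850 | 0.950 |
| Delirium off the path (*h* = 1, *d* = 0.85), no common cause | 0.850 | 0.850 |

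At 35% versus 30.3% delirium with *h* = 3, the pattern is the same and the shifts are smaller: 0.945 to 1.000 (full mediation), 0.947 to 1.029 (with a common cause), 0.853 to 0.900 (partly direct) and 0.859 to 0.930 (partly direct with a common cause).

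**A limit on the size.** If the drug acts only through delirium incidence and no non-delirious patient dies, the mortality ratio is 0.65/0.75 = 0.867. With no common cause, it cannot go lower on these figures. An effect as large as the planned 0.85 could then not be wholly mediated by delirium, and so could not be wholly removed by adjusting for it.

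**The case against.** The strongest reply is about scope. The confirmatory test names no covariates. The unadjusted Cox estimate is described before the adjusted models, which are introduced as an addition. The interim rules use 28-day survival without mentioning adjustment. Secondary objective 1 states the overall 90-day effect first and the stratified analysis second. All of this stands: on the text, the overall effect will still be estimated.

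A reader might infer from the Abstract, which describes the Cox analyses simply as covariate-adjusted, that the delirium-adjusted model is the main analysis. The Abstract does not call it main or primary, and the statistics section points the other way. What remains is a looseness: nowhere is the primary model expressly called unadjusted.

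A reader might also infer that conditioning on delirium must remove or reverse the effect. The table shows otherwise. Complete removal needs full mediation, and reversal in these settings came from a common cause of delirium and death. A direct effect is diluted. Nothing changes if delirium is off the path and no common cause exists, although that case contradicts the trial's rationale.

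The time-dependent bias is not quantified here. The article does not say whether delirium enters as fixed or time-dependent, and the Ethics section puts average onset at day 2 after ICU admission, so this part may be modest.

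None of this defends including delirium in the covariate list.

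**Conclusion.** The point holds for the adjusted survival analyses and for the 90-day analysis stratified by delirium. Neither estimates the effect of prophylaxis, because both condition on an outcome of treatment that the trial places on the path to lower mortality. The primary 28-day Cox comparison is not shown to be affected.

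On the article's 75% versus 65% delirium and 12% placebo mortality, the possible shift runs from a dilution of roughly 0.07 to 0.10 on the hazard-ratio scale (0.827 to 0.900; 0.850 to 0.950) to a sign change of up to 0.13 (0.955 to 1.085). These sizes depend on the assumed delirium–death hazard ratio, direct effect and common cause, so they are illustrations and not forecasts. That the analyses target the wrong quantity follows from the article's own definitions and does not depend on those assumptions.

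**What to change.** 1. Remove delirium from the covariate list for 28-day and 90-day survival. Adjust only for prespecified baseline covariates: APACHE-II score, age, sex, sepsis if present at baseline, and PRE-DELIRIC score, which carries baseline delirium risk.
2. State that the primary Cox test does not condition on delirium, and bring the Abstract's description into line.
3. Delete the delirium-stratified 90-day analysis. Alternatively, relabel it exploratory, with delirium as a time-dependent variable and no treatment claim resting on it.

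The cost is a few sentences. The PRE-DELIRIC score, APACHE-II score, age and sex are already collected. The sample size does not change. The change should be settled before unblinding.

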### Ethics

The study will be conducted according to the principles of the Declaration of Helsinki (version 2008) and in accordance with the Medical Research Involving Human Subjects Act.

There are indications that early treatment of delirium is more effective than delayed treatment [37], but this needs to be confirmed in other studies. Since it is recognized that the onset of delirium occurs, on average, on day 2 after ICU admission, early preventive treatment is likely to be more effective. In the short-term, low dose haloperidol has no known relevant side effects, therefore randomization and administration of study medication will be started immediately following identification of a high-risk patient. When an informed consent procedure results in a delay of randomization, a deferred consent procedure may be followed. The informed consent procedure will be started as soon as possible, but always within 24 h following ICU admission. If no deferred informed consent can be obtained within 24 h, the patient will be excluded from the study and study drug administration will be stopped.

The medical ethical committee of Arnhem-Nijmegen (CMO) approved this study including this deferred consent procedure (CMO-number 2012/424). This trial is registered on clinicaltrials.gov: NCT01785290.

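### Dosed patients without deferred consent at 24 h leave the study, so deaths before consent can be lost from a 28-day survival endpoint described as intention-to-treat

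*Protocol article*

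**What the plan says.** All references are to the protocol article.

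- **Ethics, timing.** "randomization and administration of study medication will be started immediately following identification of a high-risk patient". Where seeking consent would delay randomisation, consent may be deferred.
- **Ethics, failed consent.** "If no deferred informed consent can be obtained within 24 h, the patient will be excluded from the study", and the study drug is then stopped.
- **Study population, Inclusion criteria.** Eligible patients are those "with an expected length of ICU stay of over one day will be included", subject to consent. After inclusion, patients "who do not receive any study drug and are discharged from the ICU within 24 h will be discarded from further analysis". By contrast, "Patients who received at least one dose will remain in the study".
- **Study population, Exclusion criteria.** The list opens with absence of informed consent and later has "ICU-stay less than one day", without the word expected.
- **Sample size calculation and statistics.** "Data will be analyzed according to the intention-to-treat principle". Table 1 likewise says that every patient is classed as alive or dead at day 28 by intention-to-treat.

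The article does not say which of these statements prevails, or how to handle a patient who is dosed and dies before consent has been obtained.

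**The concern.** Membership of the primary analysis set should not depend on anything that happens after randomisation, least of all on the outcome. Under the deferred-consent rule it can. Death in the first hours may itself be the reason that consent is never obtained, and the patient then drops out of a survival analysis because of the event being counted. These are also the deaths closest in time to the first doses.

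The second problem is that the set is not uniquely defined. One analyst, following the Study population section, keeps a dosed patient without consent; another, following the Ethics section, removes the same patient. Their denominators and death counts differ, and both can point to the text.

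**Working it through.** **1. The statements applied to individual patients**

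| Patient | Ethics rule | Study population rules | Intention-to-treat |
|---|---|---|---|
| Dosed, dies at hour 12, no consent yet | excluded if consent is not obtained by 24 h | kept (received a dose); out if the ICU-stay exclusion is applied to actual stay | kept |
| Dosed, alive, no consent at 24 h | excluded | kept if the dose rule is read literally | kept |
| Consent given, undosed, discharged within 24 h | not affected | discarded | kept |
| Consent given, dosed, discharged within 24 h | not affected | kept; out if the ICU-stay exclusion is applied to actual stay | kept |

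The first row matters most for the endpoint. The third removes only patients who are alive at that point and have had no study drug, so it is a smaller departure. The rule that keeps dosed patients agrees with intention-to-treat and does not clash with the rule on undosed discharges.

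**2. The plan's own numbers**

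Inputs: 715 patients per arm (Sample size calculation and statistics); 12% anticipated placebo mortality (Abstract), taken here as 28-day mortality.

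- Total: 3 × 715 = 2,145, as stated.
- Dropout allowance: 647 × 1.1 = 712 and 647 / 0.9 = 719; the stated 715 lies between. The sample size is not at issue here.
- Expected deaths per arm: 0.12 × 715 = 85.8.

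**3. Deaths exposed to the rule**

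The article gives neither the number of first-day deaths nor the number of consent failures. Assuming a constant hazard over 28 days:

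- Daily hazard: −ln(1 − 0.12) / 28 = 0.00457.
- First-day probability of death: 1 − exp(−0.00457) = 0.00456.
- First-day deaths per arm: 715 × 0.00456 = 3.3; over three arms, 2,145 × 0.00456 = 9.8.
- Share of expected deaths: 3.3 / 85.8 = 3.8%, about 4%.

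These deaths are exposed to the rule, not necessarily lost: only those without consent would go. Mortality concentrated in the first days would raise the figure.

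**4. What such a loss could do**

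Suppose all 3.26 first-day deaths (3.3 before rounding) were removed from an arm.

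- Observed mortality: (85.8 − 3.26) / (715 − 3.26) = 11.6% instead of 12%.
- If this happened in one arm only, with no true effect, the apparent hazard ratio would be ln(1 − 0.116) / ln(1 − 0.12) = 0.96.
- If it happened equally in all arms, the comparison would hardly move.

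For wider assumptions, removing 5%, 10% or 20% of deaths from one arm only would give apparent hazard ratios of 0.95, 0.91 and 0.81. Nothing in the article points to losses of that size or to their falling in one arm.

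**The case against.** The strongest reply is that the passages can be read together. The inclusion paragraph makes inclusion conditional on consent, and absence of consent heads the exclusion list. The rule keeping dosed patients follows a sentence about patients already included, so it may cover only those who consented, with the Ethics section dealing with the rest. That is a fair reading, and it softens the contradiction between those two sections. It does not remove the conflict with intention-to-treat, because the patients concerned have been randomised and may have been dosed.

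The ICU-stay exclusion is most naturally loose wording for expected stay. Eligibility is defined by expected stay elsewhere, and the separate rules for stays under 24 h would have little purpose if every such stay were excluded. A reader might infer that this criterion is a second route by which dosed first-day deaths disappear. The text allows that only if taken literally, although the same list does use the word expected for survival.

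A reader might also infer that early harm would be hidden or the comparison biased. The article does not support that. Ampoules are identical and treatment is double-blind, so losses should be roughly balanced. The monitoring board is unblinded, and deaths that the investigator attributes to the drug are collected. Whether excluded patients stay in the board's data is not stated.

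Patients thought unlikely to survive two days are excluded, which lowers early mortality, and deferred consent applies only where seeking consent would cause delay. Both argue for a small number.

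Finally, the ethics committee approved the deferred-consent procedure, so using data without consent is not a free statistical choice. That stands, and it limits the fix. Detailed analysis sets may also be left to a fuller document, but such a document would still have to override a rule stated here.

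**Conclusion.** The point holds. The deferred-consent rule can remove randomised, dosed patients, including those who die before consent, from a 28-day survival analysis described as intention-to-treat. Discarding undosed early discharges is a lesser departure, and the ICU-stay exclusion is a wording fault that could be misapplied after randomisation.

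The likely size is small. About 3.3 deaths per arm, or about 4% of about 86, are exposed on day 1, and fewer would be lost. This rests on 12% mortality at 28 days and a constant hazard; the share without consent at death is unknown. A reader might infer that four rules all contradict one another, or that a much larger share of primary events is at risk. The article supports neither. Differential bias is possible but not shown. What is established is an analysis set that the text does not define uniquely and that can depend on the outcome.

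**What to change.** 1. Define the primary analysis as all randomised patients, by allocated arm, with vital status at day 28, except those whose data may not be used for lack of consent. Reconcile Study population, Ethics, Table 1 and the statistics section with that definition.
2. Reword the exclusion criterion to an expected ICU stay of less than one day.
3. Keep undosed early discharges in the primary analysis, and remove them only in a sensitivity analysis.
4. Ask the ethics committee whether the vital status of patients who die before deferred consent may be retained.
5. If it may not, call the set modified intention-to-treat. Report post-randomisation exclusions and deaths by arm as far as permitted, including to the monitoring board, and run a sensitivity analysis that counts them. If only totals by arm may be used, these patients can be entered as day-1 deaths.

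The cost is some rewording, one query to the ethics committee, and slight dilution of the treatment effect from a few undosed patients. The number randomised stays at 715 per arm.
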